### Objectives

1.3

The primary objective of this study is to evaluate the proportionate reduction in the occurrence of severe RIOM, as assessed using RTOG grading scale, among participants receiving a Siddha regimen as an adjunct to standard care compared with those receiving standard care alone, assessed during radiotherapy and at six weeks post-radiotherapy.

The secondary objectives are to assess the proportionate reduction in the severity of radiation-induced oral mucositis using WHO oral mucositis scale at the same time points; to compare oral cavity pain intensity between the study groups using VAS, assessed weekly throughout the study period; to evaluate changes in analgesic usage, including escalation or de-escalation according to the WHO Three-Step Analgesic Ladder, on a weekly basis during the study period; to estimate and compare the proportion of adverse reactions between the study groups; and to evaluate differences in the frequency and duration of treatment interruptions attributable to oral mucositis between the study groups.

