#### Inclusion criteria

2.3.1

Participants aged 20–75 years of any gender, diagnosed with head and neck cancers involving the oral cavity and/or oropharynx and scheduled to undergo radiotherapy for a period of 4–7 weeks with a total radiation dose of 55–72 Gy, will be eligible for inclusion in the study. Only those who are willing to participate and are willing to provide written informed consent before the enrolment, will be included.

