#### Comparator description

2.4.2

Participants in Arm B will receive SOC alone for the management of RIOM, as described in the intervention arm. Additional topical anaesthetic and anti-inflammatory gels will be provided for oral mucositis of grade ≥ 2 in accordance with institutional protocol.

Assessments will be conducted weekly, in parallel with the intervention arm, until 6week post radiotherapy or until recovery, whichever occurs earlier. Treatment adherence will be monitored by the oral hygiene coordinator, staff nurse, and investigators, with family caregivers trained during the radiotherapy admission period to assist in monitoring during the post-radiotherapy phase. Trial interventions will be administered for 10–13 weeks, depending on the required radiation dose (Gy) based on tumour size and severity. Recovery will be defined as Grade 0 oral mucositis on both RTOG and WHO oral mucositis scales. All participants will receive radiotherapy using a linear accelerator (LINAC) with three-dimensional conformal radiotherapy (3DCRT) for a duration of 4–7 weeks, in accordance with institutional practice. Before initiation of radiotherapy, all participants will undergo a baseline oral examination and receive necessary dental care, wherever feasible, according to institutional standard dental care protocols. Standardized oral hygiene instructions will be provided and reinforced uniformly throughout the study period in both study arms.

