### Outcomes

2.5

The primary outcome of the study is the severity of RIOM, assessed using RTOG grading scale. This will be measured as the proportion of participants who develop severe oral mucositis (RTOG grade ≥ 3) at any time during radiotherapy and up to six weeks following completion of radiotherapy, compared between the two study arms. The primary outcome will be assessed from randomisation until the last day of study medication use.

The secondary outcomes include oral mucositis severity assessed using WHO oral mucositis scale, measured as the proportionate reduction in the occurrence and severity of mucositis during radiotherapy and up to six weeks post-radiotherapy. Oral cavity pain, evaluated using VAS as the proportion of participants achieving a minimum two-point reduction in pain intensity and analgesic usage, assessed as the percentage of participants requiring analgesics categorised according to WHO three-step analgesic ladder. Safety outcomes will be evaluated by documenting the number of adverse events reported in each study group. Treatment interruption will be assessed as the proportion of participants experiencing one or more radiotherapy interruptions due to severe RIOM and the total number of days of missed radiotherapy. In addition, body weight changes during radiotherapy, requirement for nasogastric tube feeding, and interruptions in oral intake will be documented as exploratory indicators of nutritional impact. All secondary outcomes, except treatment interruption, will be assessed from randomisation until the last day of study medication use, while treatment interruption will be evaluated until the completion of radiotherapy.

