### Participant timeline

2.6

Participants will undergo initial screening and randomisation at baseline, followed by a 14-week observation period comprising weekly clinical evaluations and periodic laboratory assessments as detailed in the timeline below (Table 2).

**Table 2 T2:** Schedule of enrolment, interventions, and assessments.

Activity/Assessment	Baseline	W1	W2	W3	W4	W5	W6	W7	W8	W9	W10	W11	W12	W13
Enrolment														
Screening & Informed Consent	X													
Randomisation & Allocation	X													
Intervention														
Study Intervention	X	X	X	X	X	X	X	X	X	X	X	X	X	X
Efficacy Assessment														
RTOG Scale	X	X	X	X	X	X	X	X	X					X
WHO oral mucositis Scale	X	X	X	X	X	X	X	X	X	X	X	X	X	X
VAS		X	X	X	X	X	X	X	X	X	X	X	X	X
WHO 3-step analgesic ladder		X	X	X	X	X	X	X	X	X	X	X	X	X
Interruption of RT		X	X	X	X	X	X	X	X					
Days of Missed RT		X	X	X	X	X	X	X	X					
Safety & Laboratory Assessment														
Safety Monitoring		X	X	X	X	X	X	X	X	X	X	X	X	X
CBC	X								X					X
LFT	X								X					X
RFT	X								X					X

RT, radiotherapy; RTOG, Radiation Therapy Oncology Group; WHO, World Health Organization; VAS, visual analogue scale; CBC, complete blood count; LFT, liver function test; RFT, renal function Test; W1−13, No. of week.

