### Ancillary and post-trial care

6.5

After completion of RT period, participants in both study arms will be followed for an additional 6weeks, during which the assigned treatments will be continued. Follow-up assessments will be conducted weekly via telephone to monitor recovery and document relevant outcomes.

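### The radiotherapy-interruption outcome is narrower than its objective: it counts only interruptions for severe mucositis and leaves the cause of missed days unstated

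*Protocol article*

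**What the plan says.** Section 1.3 (Objectives) sets out to compare the "frequency and duration of treatment interruptions attributable to oral mucositis between the study groups". It attaches no grade to the mucositis.

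Section 2.5 (Outcomes) defines the matching outcome in two parts: the proportion of participants with one or more "radiotherapy interruptions due to severe RIOM and the total number of days of missed radiotherapy". Earlier in the same section, severe is defined as RTOG grade 3 or higher, which is the primary endpoint. On timing, section 2.5 adds that "treatment interruption will be evaluated until the completion of radiotherapy".

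In section 2.6, Table 2 has a row for "Interruption of RT" and a row for "Days of Missed RT". Both are marked W1 to W8 and blank from W9 to W13.

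Eligible patients are "scheduled to undergo radiotherapy for a period of 4–7 weeks" (section 2.3.1).

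**The concern.** An objective and its outcome should name the same event. Here they differ on cause. The objective takes in any interruption put down to oral mucositis, while the outcome keeps only those put down to severe disease. The duration part of the outcome names no cause at all, although the objective asks for duration attributable to mucositis.

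The restriction matters beyond lost events because grade 3 is the line the regimen is expected to move patients below. A participant whose mucositis falls from grade 3 to grade 2, and whose radiotherapy is still interrupted for it, drops out of the count although treatment was interrupted all the same.

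Section 8 names fewer treatment interruptions among the results that would support the regimen, and section 7 presents their evaluation as part of the study's value. Two written definitions would leave a choice to be made once data are in hand.

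**Working it through.** **1. Definitions side by side**

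| Element | Objective (1.3) | Outcome (2.5) |
|---|---|---|
| Cause of interruption | Oral mucositis, any grade | Severe RIOM (RTOG ≥3) |
| Frequency measure | Frequency of interruptions | Proportion with one or more |
| Duration measure | Duration attributable to mucositis | Total missed days, cause not stated |

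An interruption for grade 1–2 mucositis is counted in the middle column and not in the right-hand one.

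The missed-days phrase can be read in two ways. If the severe restriction carries over to it, days lost at grade 1–2 are left out. If it does not, days missed for reasons unrelated to mucositis are included. Neither reading matches the objective.

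**2. How the restriction can create a difference between arms**

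Suppose each arm has n participants, of whom the same number m are interrupted for mucositis. Let g_A and g_B be the shares of those m whose mucositis is grade 3 or higher in arms A and B.

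- Objective's definition: m/n − m/n = 0.
- Section 2.5 definition: (m/n)(g_B − g_A), which is above zero whenever g_A < g_B.

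So the arms can differ on the outcome with no difference in mucositis interruptions. The share of interruptions left out in an arm is 1 − g. The documents give no value for g, so this share could lie anywhere from 0 to 1.

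**3. Collection window**

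The plan's own durations reproduce. Radiotherapy of 4–7 weeks plus the 6 weeks of follow-up in section 6.5 gives 4 + 6 = 10 and 7 + 6 = 13, in line with "Trial interventions will be administered for 10–13 weeks" in section 2.4.2.

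Slack before the W8 marks end = (8 − planned weeks) × fractions per week. The documents do not give fractions per week. I assume 5, with 6 as an upper value.

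| Planned course | Slack at 5 per week | Slack at 6 per week |
|---|---|---|
| 4 weeks | 20 treatment days | 24 |
| 5 weeks | 15 | 18 |
| 6 weeks | 10 | 12 |
| 7 weeks | 5 | 6 |

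Every course delivered as planned ends within the marked weeks, with at least one week to spare. A 7-week course passes W8 only after more than 5 (or 6) missed treatment days, or somewhat fewer if radiotherapy starts late in W1. The days that caused the delay up to then fall inside W1–W8 and have recording points. Only fractions missed in W9 or later lack one.

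**The case against.** The best defence is that the mismatch is one of wording and may be small in effect. Sections 1.1 and 7 both link treatment interruption to severe mucositis, so few interruptions may occur at lower grades. If missed days are read as unrestricted, they already capture duration at every grade, and only the yes/no proportion is narrowed. This stands as a limit on size and is why the outcome answers the objective in part. It does not remove the mismatch, since unrestricted days are not attributable to mucositis either.

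On the window, the text of section 2.5 runs to the end of radiotherapy, section 4.1 has weekly assessment throughout the course, and section 4.3 checks case record forms against source records. A reader might infer that week 8 is a third, conflicting counting rule, or that the most delayed participants lose their missed days. Neither is supported: W8 is a collection schedule that fits every planned course, and only days missed after it are exposed.

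A reader might also infer that a treating team aware of allocation decides which interruptions are due to mucositis. The documents do not say who makes that attribution, and section 3.4 provides for outcome assessors unaware of allocation. That charge cannot be made from the text.

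**Conclusion.** The point holds as a mismatch between a secondary objective and its outcome. Following section 2.5 omits interruptions for grade 1–2 mucositis that section 1.3 asks for, and leaves missed days without a stated cause. It would go too far to say that the outcome fails to answer its objective: it answers it for severe disease. The size of the omission is unknown because the documents give no grade breakdown of interruptions.

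The Table 2 gap is minor and conditional. It needs a course running past W8 (more than about 5 missed treatment days on a 7-week plan, at an assumed 5 fractions per week) and then a further missed fraction.

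This is a low-severity point that is cheap to correct.

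**What to change.** - In section 2.5, use the objective's cause, oral mucositis of any grade, for both the proportion interrupted and the missed days.
- Record each missed fraction with its cause until the last fraction is delivered.
- Change the two Table 2 rows to weekly until last fraction.
- Report all-cause interruptions and all-cause missed days by arm beside the attributed figures. The all-cause figures do not depend on anyone's judgement of cause.

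The cost is minor wording in section 2.5 and Table 2, plus one extra results table. Since enrolment has begun, the definition should be settled before any results by arm are examined. The change concerns measurement only and alters no treatment rule.

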### Participant timeline

2.6

Participants will undergo initial screening and randomisation at baseline, followed by a 14-week observation period comprising weekly clinical evaluations and periodic laboratory assessments as detailed in the timeline below (Table 2).

**Table 2 T2:** Schedule of enrolment, interventions, and assessments.

Activity/Assessment	Baseline	W1	W2	W3	W4	W5	W6	W7	W8	W9	W10	W11	W12	W13
Enrolment														
Screening & Informed Consent	X													
Randomisation & Allocation	X													
Intervention														
Study Intervention	X	X	X	X	X	X	X	X	X	X	X	X	X	X
Efficacy Assessment														
RTOG Scale	X	X	X	X	X	X	X	X	X					X
WHO oral mucositis Scale	X	X	X	X	X	X	X	X	X	X	X	X	X	X
VAS		X	X	X	X	X	X	X	X	X	X	X	X	X
WHO 3-step analgesic ladder		X	X	X	X	X	X	X	X	X	X	X	X	X
Interruption of RT		X	X	X	X	X	X	X	X					
Days of Missed RT		X	X	X	X	X	X	X	X					
Safety & Laboratory Assessment														
Safety Monitoring		X	X	X	X	X	X	X	X	X	X	X	X	X
CBC	X								X					X
LFT	X								X					X
RFT	X								X					X

RT, radiotherapy; RTOG, Radiation Therapy Oncology Group; WHO, World Health Organization; VAS, visual analogue scale; CBC, complete blood count; LFT, liver function test; RFT, renal function Test; W1−13, No. of week.

### Sample size

2.7

A study by Kazemiana *et al*. reported that among patients with head and neck cancer receiving benzydamine for the management of RIOM, the occurrence of severe RIOM was 43.6%, compared with 78.6% in the placebo group. Based on findings from our previous unpublished study, a 52% reduction in RIOM grade was observed after 48 days of treatment with TPC mouthwash and GV oral application, and a separate study evaluating TPC with povidone–iodine reported an RIOM occurrence of 10%. Drawing on these findings and clinical expertise, it is assumed that the addition of Siddha regimen to SOC would result in a 15% relative reduction in the occurrence of RIOM compared with SOC alone. Accordingly, assuming a 15% superiority margin, a two-sided significance level of 5%, and 80% power, the calculated sample size is 64 participants per arm. Allowing for an anticipated 20% dropout rate, 80 participants per group will be recruited, resulting in a total sample size of 160 participants. The formula to calculate superiority of proportion is given below.$$m=\frac{\left(Z\;1\;-\alpha +Z\;1-\beta )\;2\;[\pi S\;(1-\pi S\;)+\pi T\;(1-\pi T\;)\right]}{(\pi T\;-\pi S\;-\delta )\;2}$$where,
*δ*: Superiority limit of the difference in Proportionsπ T: Proportion in Test Treatmentπ S: Proportion in Standard Treatmentπ T – π S: Expected difference in proportions*α*: Significance level1 – *β*: Power

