### Randomisation & sequence generation

3.1

Participants will be randomised in a 1:1 allocation ratio to receive either the Siddha regimen with SOC or SOC alone using block randomization with randomly varying block sizes. The randomisation sequence will be generated by an independent statistician using validated online randomisation software. Although randomisation will not be stratified, predefined subgroup analyses based on treatment modality to cancer, will be conducted during outcome analysis to explore potential differential treatment effects across these subgroups.

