The present study is designed as a randomised controlled Phase II superiority trial. One of its major strengths is the use of multiple validated tools for comprehensive assessment of RIOM. RTOG and WHO oral mucositis grading scales provide physician-based evaluation of mucosal severity and functional impairment, while the VAS captures patient-reported pain. In addition, WHO analgesic ladder reflects the need for analgesic support related to RIOM pain. Together, these measures allow a multidimensional assessment of disease severity and progression. Weekly assessments during radiotherapy and follow-up will help to closely monitor changes in mucositis severity and recovery over time. The study also evaluates treatment interruptions, an important but often under-reported consequence of severe RIOM that may affect overall treatment outcomes.

Certain limitations of the study should also be considered. Since the trial follows an open-label design, there is a possibility of performance and reporting bias. However, the use of standardised assessment scales, blinded outcome assessment and evaluation by trained oncology professionals are expected to minimise this risk. In addition, published evidence on interventions comparable to the present Siddha regimen for RIOM is limited. Although preliminary institutional observations were referenced to provide contextual understanding, they were not used as formal evidence or assumptions for sample size estimation. The study may also encounter certain clinical and assessment-related challenges during the study period. Some participants may require NG tube feeding of liquid food due to conditions such as tumour obstruction, nutritional compromise, postoperative status, or severe RIOM, which may lead to overestimation of severity grading, particularly with WHO oral mucositis scale. Similarly, additional supportive medications administered according to institutional protocols and cancer-related complications may affect symptom severity and outcome assessment. These factors will be carefully documented and considered during analysis.

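### The 64 per arm in section 2.7 does not follow from its stated assumptions: for a 15% relative reduction from 43.6%, the planned two-sided test has about 11–12% power, not 80%

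*Protocol article*

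**What the plan says.** Section 2.7 (Sample size) starts from a published study in which, with benzydamine, "the occurrence of severe RIOM was 43.6%, compared with 78.6% in the placebo group". It also mentions the sponsor's unpublished series, in which "a 52% reduction in RIOM grade was observed after 48 days of treatment with TPC mouthwash and GV oral application", and a further study with a 10% occurrence. From these and clinical judgement, "it is assumed that the addition of Siddha regimen to SOC would result in a 15% relative reduction in the occurrence of RIOM". It continues: "assuming a 15% superiority margin, a two-sided significance level of 5%, and 80% power, the calculated sample size is 64 participants per arm". Then: "Allowing for an anticipated 20% dropout rate, 80 participants per group will be recruited", 160 in total.

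The printed formula has the sum of Z at 1−α and Z at 1−β, squared, in the numerator, and the square of πT − πS − δ in the denominator, where δ is the superiority limit. The section does not say which πS and πT were entered, which sign δ took, or which value of z was used.

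Section 4.5 (Statistical methods) plans a chi-square or Fisher's exact test at a two-sided 5% level and mentions no margin. The Discussion (section 7) says of the preliminary institutional observations that "they were not used as formal evidence or assumptions for sample size estimation".

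**The concern.** Section 2.7 fixes an effect, a margin, a significance level, a power and a sample size, and prints the formula linking them, so they can be checked against each other. Three things look wrong.

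- A 15% relative reduction from a rate near 44% is only 6 to 7 percentage points, and 64 per arm is far too few to detect that.
- A superiority margin of 15 points is larger than the benefit expected.
- The formula's Z at 1−α is one-sided if α is 5%, while the text says two-sided.

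If the power claim is wrong for the effect the plan says it assumes, the trial would usually miss that effect. A non-significant result would then have to be read against a claimed 80% power that the design does not have for it.

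**Working it through.** **Inputs**

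- Control rate πS = 0.436, the cited severe-RIOM rate on benzydamine (section 2.7). Using it as the control rate is an inference; benzydamine is the standard-care rinse (section 2.4.1, Table 1).
- Assumed effect: 15% relative, so πT = 0.85 × 0.436 = 0.3706. Difference 0.0654, or 6.5 points.
- α = 5%, stated as two-sided; power 80%; δ = 0.15, sign not given.
- (1.645 + 0.842)² = 6.183 with a one-sided z; (1.960 + 0.842)² = 7.849 with a two-sided z.
- Variance term: 0.436 × 0.564 + 0.3706 × 0.6294 = 0.2459 + 0.2333 = 0.4792.

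**1. Can 64 be reproduced from the stated effect?** Using m = (z-sum)² × 0.4792 / (πT − πS − δ)²:

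| δ | Denominator | One-sided z | Two-sided z |
|---|---|---|---|
| 0 | 0.0654² | 693 | 879 |
| +0.15 | 0.2154² | **63.85** | 81.1 |
| −0.15 | 0.0846² | 414 (not valid) | 525 (not valid) |

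Only δ = +0.15 with the one-sided z gives 64. Because severe mucositis is a harm, πT − πS is negative, so δ = +0.15 adds the margin to the benefit. That is the form of a non-inferiority calculation. With the superiority sign (δ = −0.15), the expected 6.5-point benefit falls short of the 15-point margin. The bottom-row figures are then not usable sizes, because squaring hides the wrong direction; power for that test at 64 per arm is below 0.5%.

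**2. Other routes to about 64 from rates in the same section**

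- 78.6% against 43.6%, δ = −0.15, one-sided z: 6.183 × (0.1682 + 0.2459) / (0.35 − 0.15)² = 64.0.
- 52% read as a reduction in the rate (43.6% to 20.9%), no margin, two-sided 5%: 62.8 with unpooled variance, 66 with pooled variance.

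**3. Power of the planned test for the stated effect**

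At 64 per arm the standard error of the difference is √(0.4792/64) = 0.0865. Then 0.0654/0.0865 = 0.756, and power ≈ Φ(0.756 − 1.960) = Φ(−1.204) = 11.4%. The pooled-variance version gives 11.3%, and counting both tails gives 11.8%. At 80 per arm power is about 13%. For 80% power, 879 (unpooled) to 883 (pooled) per arm are needed.

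**4. Sensitivity to the control rate** (15% relative reduction, 64 per arm, two-sided 5%)

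| Control rate | Power |
|---|---|
| 30% | 8–9% |
| 43.6% | 11–12% |
| 50% | 13–14% |
| 70% | 24% |
| 78.6% | 32% |
| 90% | 53–55% |

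**5. If 15 percentage points was meant** (43.6% against 28.6%): 42–43% power at 64 per arm; 157 to 160 per arm needed.

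**6. What 64 per arm does deliver:** 80% power for 43.6% against 20.7%, a relative reduction of about 53% (22.9/43.6).

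**7. Dropout:** 64/(1 − 0.20) = 80, which is correct.

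**The case against.** The strongest reply is that the section never reports what was entered. A reader might infer from step 1 that the margin was given the wrong sign and that the trial was in effect sized as a non-inferiority study. The documents do not support that as a finding. The two routes in step 2 also reach about 64, one of them with a correctly signed margin, and the full protocol behind the article may record the actual inputs. The sign error is plausible but unproven.

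Neither alternative rescues the stated power, however. The first sets placebo against benzydamine, which is not this trial's comparison, and still uses a one-sided z. The second turns a reduction in grade into a reduction in rate and relies on a series that the Discussion says was not used for this purpose. Neither uses the 15% effect.

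It is also fair to say that 12% is conditional. Section 2.7 never names 43.6% as the design rate, and its assumed reduction is in occurrence of RIOM without the word severe. Section 2.5 counts grade 3 or worse, while section 4.5 counts grade 2 or worse. The control rate could therefore be well above 43.6%, so the figure needs its range.

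Finally, a reader might conclude that the trial has no useful power at all. That goes too far: 64 per arm is adequate for a roughly 53% relative reduction from 43.6%, close to the 52% cited in section 2.7 if that could be read as a rate. The documents do not settle whether the effect's wording or the sample size is the mistake.

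**Conclusion.** The point holds in this form: 64 per arm does not follow from a 15% relative reduction at two-sided 5% and 80% power. With 43.6% as an inferred control rate, the planned test has about 11–12% power at 64 per arm and 13% at 80, and about 880 per arm would be needed. Over control rates from 30% to 90%, power at 64 per arm stays between about 8% and 55%, so the shortfall stands throughout that range. Reading 15% as absolute points from 43.6% gives only 42–43%.

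Two conflicts hold whatever the source of the 64. If α is 5%, the printed one-sided z contradicts the two-sided level. And, from 43.6%, a 6.5-point benefit cannot exceed a 15-point superiority margin, which the planned test does not use in any case. How 64 was obtained remains open.

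The conflict between sections 2.7 and 7 over the unpublished series is a separate matter of consistency and does not affect these power figures.

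**What to change.** Keep 160 participants and rewrite section 2.7:

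1. State πS, πT, the sign of δ and the z that were used. Then make the calculation agree with the two-sided, margin-free test in section 4.5 by removing the margin and the one-sided z.
2. Replace the 80% power claim with what the size delivers: at 64 evaluable per arm, 80% power for about 43.6% against 21%, and about 12% for a 15% relative reduction from 43.6%, with the range over control rates shown above.
3. Commit to reporting the risk difference with its 95% confidence interval, so that a non-significant result shows which effects remain possible.
4. Separately, reconcile section 2.7, which draws on the unpublished series, with the Discussion, which says it was not used for sample size estimation.

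The cost is a rewrite of one section, one sentence to reconcile in the Discussion, and a less favourable power statement. No patients are added. If the sponsor does intend to detect a 15% relative reduction from 43.6%, rewording will not achieve it: that needs about 880 evaluable per arm, or about 1,100 recruited per arm at 20% dropout (883/0.80 = 1,104).
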